#### Physical function

Objective outcomes will include physical domains in balance, lower extremity muscle endurance and strength, mobility level, a subjective measure to assess changes in health-related physical activity, and motor impairment level. The TUG test assesses dynamic balance ability and mobility. The participants will be required to stand up from a chair, walk 3 m, turn around, walk back to the chair, and sit down. The time to complete the TUG test has been shown to be a good indicator to detect potential fallers in frail elderly individuals [46]. The test-retest reliability of TUG in individuals with stroke was excellent [47].

The 6-Minute Walk Test (6MWT) measures the maximum distance walked over 6 minutes, which assess the endurance and mobility level of the participants. The participants can rest as needed during the test. The test-retest reliability and responsiveness have been established to be high for patients with chronic stroke [48].

Accelerometers will be used to provide an objective measure of the amount of arm movements in real-life situations (i.e., the mobility level). The participants will be asked to wear an Actigraphy activity monitor (ActiGraph, Shalimar, FL, USA) on both wrists for 3 consecutive days before and after training to measure the number of moves each minute and the average counts of move per minute. The participants will be required to wear the device during the day except for doing water-based activities such as bathing or swimming. Data recorded by the Actigraphy will be analyzed with the MAHUFFE software (http://www.mrc-epid.cam.ac.uk/). The use of the Actigraphy to measure arm use and physical activity has been established in patients with stroke [49].

The International Physical Activity Questionnaires (IPAQ) is an international measure of health-related physical activity. The short-form version of the Chinese IPAQ will be used to assess changes in physical activity before and after the intervention. The reliability and validity of IPAQ have been established in 12 countries [50, 51].

The 33-item upper limb subscale of the FMA will be used to assess motor impairments. Items are scored on a 3-point ordinal scale (0 = cannot perform, 1 = performs partially, 2 = performs fully), with a total of score of 66. Proximal shoulder/elbow and distal hand/wrist subscores will be calculated. The reliability, validity, and responsiveness of the FMA, and the clinically important differences when using the FMA have been well-established in stroke patients [52, 53].

The Rivermead Mobility Index (RMI) evaluates the participant’s bed mobility, postural transfers, and walking ability. It contains a 15-item scale that includes 14 questions and 1 direct observation, with a total of score of 15. The RMI has been shown to have excellent correlation with the Functional Independence Measure (FIM) and the Barthel Index [54].

Finally, we will evaluate lower extremity muscle strength (e.g., isometric knee flexors and extensor muscle strength) and the grip strength of the affected and less affected hand using a handheld dynamometer. During the lower extremity examination, the participant will be seated upright in a chair with back support and the knee will be placed in 90° flexion. The evaluator will stabilize the participant to eliminate synergistic movements. Participants will be asked to perform a maximal isometric contraction of knee flexion and extension with the affected and less affected side. The hand dynamometer will also measure grip strength while the participant is seated with the elbow at 90° flexion. We will record the mean value of three attempts of upper and lower extremity assessments.

#### Social participation and level of depression

The participant’s level of social participation will be assessed using the Community Integration Questionnaire (CIQ). The CIQ measures 15 items relevant to home integration, social integration, and productive activities [55]. The total score ranges from 0 to 29 points. The CIQ has been tested on various populations with acquired brain injuries, and test-retest reliability was excellent for chronic stroke patients with aphasia [55, 56]. The Geriatric Depression Scale (GDS) is a self-administered questionnaire used to evaluate mood and depressive symptoms, with each question requiring a yes or no response. A short form of the GDS will be used in this study to assess the participants. The reliability, internal consistency, and validity have been established to be good to excellent in patients with stroke [57].

### Analyses

We will use the chi square (χ^2^) test and analysis of variance to analyze differences in baseline characteristics and baseline outcome measures among the groups. Mixed-factor repeated-measures analysis of variance will be used to determine the intervention effect in the three groups. The within-subject factor will be time (pretest, posttest, and follow up), and the between-subjects factor will be group (COG, AE, and SEQ). Tukey’s test will be performed if a group × time interaction or a main effect is observed. Statistical significance will be set at 0.05 for all comparisons. In addition to *p* values, *η*
^2^ will also be calculated to determine the group difference for each outcome measure. Data analysis will be performed using PASW Statistics 18.0 software (SPSS Inc., Chicago, IL, USA).

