### Sample size

No published research to date has investigated the effects of combining aerobic exercise with cognitive training on cognitive functions in patients with stroke; therefore, the sample size calculation was based on the effects of a similar study conducted by Kim et al. [29]. The study investigated the effects of 4 weeks of cognitive, combined, motor dual-task training on cognitive and motor function in stroke survivors. The Stroop test, Timed Up and Go (TUG) test, 10-Meter Walk Test (10MWT), Figure-of-8 Walk Test (F8WT) and gait speed were used to measure cognitive and motor abilities and were evaluated three times (before and after training and at the 2-week follow up). The results showed that compared to the single-task training, the active control group, dual-task training improves cognitive and motor functions in stroke survivors, and these training benefits were maintained for 2 weeks.

A priori power analysis (G*Power software 3.1) was used to estimate the number of participants needed for this project. On the basis of Kim’s work [29], the estimated sample size requirement is 20 patients for each group in a three-group study design given the lowest effect size (*f* = 0.30), power of 0.80, and two-sided type I error of 0.05. Allowing for 20% attrition at the 6-month follow up, we plan to recruit 25 participants for each group, resulting in a sample size of 75 participants.

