### Secondary outcomes

#### Physiological markers

The cognitive and physical related biomarkers will be collected at baseline and immediately after the intervention programs. In particular, the level of BDNF will be a biomarker after cognitive rehabilitation, whereas the antioxidative marker, blood glucose indicator, and plasma lipid levels will be evaluated as exercise-related factors. For the assessment of BDNF, blood (8 mL) will be collected in sampling tubes and centrifuged at 2000 *g* for 20 minutes. Serum will be harvested, aliquoted, and stored at – 80 °C until analysis. The automated ferric-reducing ability of plasma assay will be implemented to measure the antioxidative marker. Serum BDNF will be quantified using an enzyme-linked immunosorbent assay (Human BDNF Quantikine Immunoassay, DBD00, R&D Systems) according to the manufacturer’s instructions. This sandwich enzyme-linked immunosorbent assay is set to measure natural and recombinant human mature BDNF in serum and plasma. All assays will be performed on F-bottom 96-well plates (Nunc, Wiesbaden, Germany).

Antioxidative markers will be used to reflect the changes in oxidative stress. In particular, we will be analyzing the total antioxidant capacity. HbA_1c_ level will be tested to investigate the relationships between blood glucose level and aerobic exercise. Last, the cholesterol ratio (total cholesterol/high-density lipoprotein cholesterol) will be evaluated to reflect the lipid level in the blood.

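### The three-level repeated-measures ANOVA discards observed data from anyone who misses a visit, and it cannot be fitted to biomarkers measured only twice

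*Protocol article*

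**What the plan says.** The Analyses section fixes the method: "Mixed-factor repeated-measures analysis of variance will be used to determine the intervention effect in the three groups". It then sets the repeated factor: "The within-subject factor will be time (pretest, posttest, and follow up". No outcome is exempted from this model.

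The Sample size section derives the recruitment target from expected loss: "the estimated sample size requirement is 20 patients for each group in a three-group study design", and then "Allowing for 20% attrition at the 6-month follow up, we plan to recruit 25 participants for each group".

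On visits, the Study design and Outcome assessment sections describe three assessments for outcomes in general. The Physiological markers section departs from this: "The cognitive and physical related biomarkers will be collected at baseline and immediately after the intervention programs". The Physical function section has accelerometers worn "for 3 consecutive days before and after training", and describes IPAQ as measuring change from before to after the intervention.

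**The concern.** A classical repeated-measures ANOVA with three time levels needs three values from each person. Someone who completes training and the post-test but misses the 6-month visit is removed from the whole analysis, including the pre-to-post comparison for which that person's data are complete. The protocol expects such losses, so this is the analysis it should plan for.

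Two things are at stake. Post-test measurements already collected go unused. The end-of-training comparison also becomes a comparison of those who remained at 6 months, which can mislead if staying depends on how well a participant responded.

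The second issue is simpler. Where an outcome has no follow-up measurement by design, no participant has three values, and the stated model has nothing to fit. This affects BDNF, antioxidant capacity, HbA1c and the cholesterol ratio. The Discussion presents the biomarkers as a feature that sets this trial apart from earlier ones.

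**Working it through.** **Inputs from the article.** 20 per group required, three groups, f = 0.30, two-sided alpha 0.05, 20% attrition by 6 months, 25 per group recruited.

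**The plan's own figure.** 20 / (1 − 0.20) = 25 per group, and 3 × 25 = 75. This reproduces. After 20% loss, 75 × 0.80 = 60 completers remain, which is 3 × 20, the planned analysable number.

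**Data discarded.** 75 − 60 = 15 participants. If all 15 leave after the post-test, 15 × 2 = 30 observed values (pretest and post-test) are dropped.

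**Precision at post-test.** The standard error of an arm difference scales with 1/√n, so the penalty is √(number observed at post-test / 60) − 1. The article does not say when within the 9 months losses occur, so three cases are shown:

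| Timing of the 15 losses (assumed) | Observed at post-test | SE ratio |
|---|---|---|
| all during training | 60 | √(60/60) = 1.00 |
| half during training | 67.5 on average | √(67.5/60) = 1.06 |
| all after the post-test | 75 | √(75/60) = 1.12 |

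A simulation of the last case (25 per arm, SD 1, correlation 0.5 between visits, 20% loss at random, 6,000 runs) gave standard errors for the post-test change contrast of 0.317 with completers and 0.282 with all data, a ratio of 1.12. At follow-up the gain was small: 0.323 against 0.311.

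**Power, as an illustration.** Read f = 0.30 as an unadjusted post-test effect and adjust for baseline with correlation r. Then λ = N × 0.09 / (1 − r²), with 2 and N − 4 degrees of freedom.

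- r = 0.5: N = 60 gives λ = 5.4/0.75 = 7.20, power 64%. N = 75 gives λ = 6.75/0.75 = 9.00, power 75%.
- r = 0.7: N = 60 gives λ = 5.4/0.51 = 10.59, power 82%. N = 75 gives λ = 6.75/0.51 = 13.24, power 90%.

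The figures for 75 are upper limits, since they need every participant to be seen at post-test. Both correlations and the reading of f are assumptions; the article does not define f in this way.

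**Bias, as an illustration.** In the same simulation the true difference between the combined arm and one single-modality arm was 0.60, and about 20% were lost after the post-test. Average post-test estimates were:

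| Loss mechanism (assumed) | Correlation | Completers | All data, likelihood |
|---|---|---|---|
| poor pre-to-post change raises loss, all arms | 0.5 | 0.52 | 0.60 |
| same | 0.7 | 0.55 | 0.60 |
| poor change raises loss in the single-modality arms only | 0.5 | 0.40 | 0.60 |
| same | 0.7 | 0.48 | 0.60 |

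**Two-visit outcomes.** On complete two-visit data, a two-level repeated-measures ANOVA and a mixed model gave the same interaction test (F = 2.821 for both). The problem here is the number of time levels, and a change of model class is not needed to solve it.

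**The case against.** **Attrition is already allowed for.** This stands. A reader might infer that deleting 15 people leaves the trial underpowered against its own plan. It does not: 60 is what the plan asked for. But recruiting more people replaces numbers; it neither recovers the unused post-test data nor removes selection.

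**The article never mentions deleting incomplete cases, and an unseen analysis plan may cover missing data.** Also true, and the absence of a missing-data section is not the complaint. The point rests on the method the article does fix, which uses only complete cases unless values are imputed.

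**The 12% is a best case for the alternative.** Correct. It needs every loss to fall after the post-test, and the article places the 20% only at the 6-month visit. The supportable range is 0 to 12%.

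**The bias is conjecture.** Partly. The arms differ in physical demand, so a reader might infer differential loss and hence bias. No arm-specific loss is given, and unequal loss rates alone do not bias a completer contrast; loss must also be related to outcome. The simulated values show what can happen, not what is expected.

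**The two-visit problem is narrower than it looks.** Agreed. A reader might extend it to accelerometry and IPAQ, but only the biomarker wording is explicit. The general statements elsewhere imply three visits, and the schedule in Fig. 2 is not available here. Nor does a mixed model cure the two-visit problem: it cannot estimate a follow-up effect that was never measured.

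**Conclusion.** The point holds in limited form. The stated ANOVA, without imputation, would exclude up to 15 of 75 participants and restrict the end-of-training comparison to those who stayed to 6 months. The cost is a post-test standard error 0 to 12% larger than necessary, according to the timing of loss, and exposure to bias if loss is related to observed response. It is not a shortfall against the planned 60. The power and bias illustrations rest on assumed correlations, an assumed reading of f and assumed loss mechanisms.

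For the four biomarkers the mismatch is certain on the text: two collections, three time levels. For accelerometry and IPAQ the text is unclear. This should be changed, and since the Trial status section reports that recruitment is continuing, there is time to do so before analysis.

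**What to change.** 1. For three-visit outcomes, make the main analysis a likelihood-based linear mixed model with pretest, post-test and follow-up all as responses, terms for visit and group-by-visit, and an unstructured covariance. Baseline should be a response: if it were only a covariate, anyone with no later measurement would still drop out. Every randomised participant with any measurement then contributes, analysed as assigned.
2. Keep the completer ANOVA as a sensitivity analysis.
3. For BDNF, antioxidant capacity, HbA1c and the cholesterol ratio, specify ANCOVA of the post-training value on baseline, or a two-level time factor.
4. State for accelerometry and IPAQ whether a 6-month measurement is taken, and bring the Outcome assessment, Physical function and Analyses sections into line.

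The cost is revised wording and modest programming, with no new data. Confirm that the named package (PASW Statistics 18.0) fits the model, or name another. The mixed model relies on data being missing at random given what was observed, which is still an assumption but weaker than the one the completer analysis needs.

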The objectives of this proposed trial are to determine the treatment effects of a sequential combination of aerobic exercise and cognitive training, compared with exercise or cognitive training alone, on cognitive function, physiological markers, daily function, QOL, physical function, and social participation. A notable difference between our study and previous studies is that this trial will investigate the physiological biomarkers and a variety of outcomes related to patient’s ADL, QOL, and social participation. The serum BDNF level has been selected to evaluate whether cognitive training can upregulate the neurotrophic and vascular growth factors, and the relationship between cognitive performance and serum BDNF levels will be assessed.

Meanwhile, because the fundamental goal of rehabilitation is to improve everyday functioning, determining the effect of cognitive training on ADL, QOL, and social participation is important. The establishment of a core set of outcome measures would be particularly helpful because these outcomes reflect the “real-life” significance of cognitive training. The trial also aims to determine the long-term treatment effects of different training protocols on these outcome measures. A 12-week intervention and a 24-week follow-up assessment can potentially provide reliable evidence on the long-term effects of the therapeutic regimen of cognitive training in stroke survivors.

Limitations of the design and implementation of the trial must also be considered. In this trial, we designed the cognitive training and aerobic exercise training groups as comparisons to a sequential combination of aerobic exercise and cognitive training rather than including a passive control group. Our primary aim in this trial is a parallel comparison of three experimental interventions rather than a comparison with conventional therapy. Hence, no control group that receives traditional cognitive training will be included.

With the global population aging and the increasing number of stroke survivors, there is growing urgency to identify the most effective methods to promote cognitive function. We believe that the information garnered from this trial will provide evidence for the potential synergistic intervention on cognitive function in stroke survivors, which is crucial to health care professionals involved in cognitive rehabilitation.

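### One group × time test over three visits covers both end-of-training benefit and durability, with no primary visit and a loose trigger for pairwise tests, so an effect at either visit can be presented as the result

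*Protocol article*

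**What the plan says.** The Analyses section of the protocol article applies a mixed repeated-measures ANOVA to the outcomes: "The within-subject factor will be time (pretest, posttest, and follow up), and the between-subjects factor will be group (COG, AE, and SEQ". With three groups and three visits the interaction has (3 − 1) × (3 − 1) = 4 degrees of freedom. Pairwise comparisons follow a stated rule: Tukey's "test will be performed if a group × time interaction or a main effect is observed". The level is also stated: "Statistical significance will be set at 0.05 for all comparisons".

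The Discussion treats durability as a further aim: "The trial also aims to determine the long-term treatment effects of different training protocols on these outcome measures". No separate test is attached to it. Study design and setting, and Outcome assessment, list the three visits without ranking them. They also time the second visit differently. The former puts it directly after the programmes; the latter, read literally, puts it 12 weeks after the intervention.

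The Sample size section bases the trial on f = 0.30 ("given the lowest effect size (*f* = 0.30") with "power of 0.80, and two-sided type I error of 0.05". It names neither the visit nor the test. Its only reference to a visit of this trial is the dropout allowance: "Allowing for 20% attrition at the 6-month follow up, we plan to recruit 25 participants for each group".

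**The concern.** There are two questions and one undirected test. The interaction can be significant because the arms differ at post-test only, at follow-up only, or at both, and significance does not show which. The pairwise rule does not settle it, since it leaves open whether groups are compared at post-test, at follow-up or on the average of visits. The report can therefore rest on whichever visit looks better, for each outcome.

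The trigger adds to this. A group main effect averages over all three visits, including the pretest, so it mixes baseline imbalance with treatment effect. A time main effect says nothing about differences between arms. Either one opens Tukey's test as the rule is worded.

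There may also be a power cost. If a benefit partly fades, the two extra degrees of freedom can cost more than the follow-up data add.

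**Working it through.** **The plan's own figure.** The dropout step reproduces: 20 / (1 − 0.20) = 25 per arm, and 3 × 25 = 75. The 20 per group does not follow from the stated inputs alone. With f = 0.30, power 0.80 and alpha 0.05:
- a one-way three-group ANOVA needs 111 in total (51% power at 60);
- a three-visit between-groups test needs 75 at a correlation of 0.5;
- a three-visit interaction in the G*Power parameterisation needs 27 at a correlation of 0.5, or 48 at 0.

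So the stated size does not reveal which visit or test was meant.

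**Inputs for the power check.** From the article: three arms, three visits, 20 completers per arm, alpha 0.05, f = 0.30. Assumed, because the article does not give them: f applies at post-test; SEQ exceeds both other arms by d = 0.636 SD, so f = d√2/3 = 0.636 × 0.4714 = 0.30; the between-visit correlations; and the share r of the benefit kept at 6 months.

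**Formulas under equal correlation ρ.**
- Post-test change, 2 and 57 df: λ = n d² (2/3) / [2(1 − ρ)].
- Interaction, 4 and 114 df: λ_int = n d² (2/3) [1 + r² − (1 + r)²/3] / (1 − ρ) = λ × 2[1 + r² − (1 + r)²/3].

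The multiplier is 1.33 at r = 1 or 0, 1.08 at r = 0.75 and 1.00 at r = 0.5. At half retention the follow-up visit adds nothing to the noncentrality, which is now spread over 4 df instead of 2. With ρ = 0.7, λ = 20 × 0.4045 × 0.6667 / 0.6 = 8.99, giving about 75% for the change test and 64% for the interaction at r = 0.5.

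**Simulation, 20,000 trials per setting, 20 per arm.** Correlations are pre–post / pre–follow-up / post–follow-up; entries are power in %.

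| Correlations | Post-test change | Interaction, 100% kept | 75% | 50% | 0% |
|---|---|---|---|---|---|
| 0.5/0.5/0.5 | 51 | 53 | 44 | 41 | 53 |
| 0.6/0.6/0.6 | 61 | 64 | 54 | 50 | 64 |
| 0.7/0.7/0.7 | 75 | 78 | 68 | 64 | 78 |
| 0.8/0.8/0.8 | 91 | 93 | 87 | 84 | 94 |
| 0.6/0.5/0.6 | 62 | 60 | 51 | 47 | 62 |
| 0.7/0.6/0.7 | 75 | 72 | 63 | 60 | 76 |
| 0.8/0.7/0.8 | 90 | 87 | 80 | 79 | 92 |

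Across these rows the loss is about 4 to 12 points at 75% kept and 7 to 15 at 50% kept. At 100% or 0% kept the difference is within about 4 points either way. A steeper fall in correlation (0.7/0.49/0.7 or 0.8/0.64/0.8) makes it worse: about 14 to 20 points at 50 to 75% kept, and 8 to 9 at full retention.

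**Which question was answered?** At 0.7/0.6/0.7 the interaction is significant in about 76% of trials when the effect exists only at post-test, and in about 72% when it exists only at follow-up.

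**Null behaviour.** The interaction alone is significant in about 5% of null trials (up to 6% under the steeper correlation patterns). Interaction or group main effect occurs in about 10%, close to 1 − 0.95² = 9.75% for two independent tests. This is how often pairwise testing is opened for one outcome; the time main effect is not counted.

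**The case against.** A prespecified group × time interaction is a conventional analysis for three visits and holds its level at about 5%. Long-term effect is a stated aim, so a test sensitive to both visits has a rationale. If a benefit appeared only at 6 months, the interaction would have about 53 to 93% power under the correlations in the table, against about 5% for a post-test primary test. The article is also condensed, and an analysis plan that is not shown may name a primary visit. All of this stands. It does not remove the problem in what the article itself fixes: the choice of test, and a trigger that names no visit and accepts a main effect.

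Two stronger readings are tempting. A reader might infer a flat loss of 11 to 15 points whenever a benefit partly fades. That figure belongs to half retention, where the interaction is at or near its weakest, combined with correlations that decline over time. The article gives neither quantity, and with full retention and equal correlations the interaction is slightly better.

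A reader might also infer a false-positive rate of about 9% from testing each visit at 0.05 and claiming either. The article does not plan ungated tests by visit. If a significant interaction were required first, the rate would be about 4 to 5%. The figure that follows from the article's wording is the 10% trigger rate.

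**Conclusion.** The point holds for the structure of the analysis: two stated aims, one omnibus test, no primary visit, and pairwise comparisons opened by an interaction or a main effect at an unspecified visit. This needs no assumption about effect size.

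The power cost is real only if the benefit partly fades, and its size is conditional. It is about 4 to 15 points at 50 to 75% retention when correlations lie between 0.5 and 0.8 and fall by no more than 0.1 over the longer gap, and it is larger if they fall faster. It should not be quoted without those conditions. The comparator is a change score, so that only the visit question is measured; adjusting for the pretest instead would add a separate gain. The change should be made, but the planned interaction is not an invalid test.

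**What to change.** In Analyses:
- Name the end-of-programme assessment as the primary time.
- Make the primary test the three-group comparison at that visit, adjusted for the pretest value (ANCOVA), at 0.05, with Tukey's comparisons at that visit only.
- Test the 6-month comparison only if the primary test is positive, and report it as durability. The fixed order costs no alpha.
- Keep the three-visit model for estimates and graphs, and remove a main effect as a trigger.

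In Sample size, say which visit and which test the 20 completers per group refer to. Reconcile the timing of the second visit between Study design and setting and Outcome assessment, since the primary time depends on it.

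The cost is a few sentences and no new data; Trial status says recruitment is still open. The real price is that a benefit appearing only at 6 months becomes a secondary finding: the primary test would have about 5% power for it, against about 53 to 93% for the interaction under the correlations in the table.

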## Methods/design

### Study design and setting

This study will be a single-blind, multisite, randomized controlled trial. After signing the informed consent, participants will be stratified by Mini-Mental State Examination (MMSE) scores and randomly assigned to the cognitive training (COG), aerobic exercise (AE), or sequential combination of aerobic exercise and cognitive training (SEQ) groups (Fig. 1) by an independent research assistant. The randomization scheme will be generated with the web-based randomization tool (available at http://www.randomizer.org/), applying block randomization to achieve three groups with a ratio of 1:1:1. All participants will receive 36 training sessions over a 3-month period. The participants will be assessed before and immediately after the intervention programs, and 6 months after the intervention programs. The evaluator for all assessments (before, after, and follow up) will be blinded to the group allocation. Figure 2 illustrates the timing of all trial processes (Additional file 1)﻿.

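### Using pretest as a level of time, and leaving the MMSE stratifier out of the model, gives up precision that baseline covariates would recover at almost no cost

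*Protocol article*

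**What the plan says.** Under Study design and setting, the protocol article says that "participants will be stratified by Mini-Mental State Examination (MMSE) scores and randomly assigned" to the three arms, "applying block randomization to achieve three groups with a ratio of 1:1:1". It gives no MMSE cut-points and no reason for choosing MMSE.

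Under Analyses, it names the model: "Mixed-factor repeated-measures analysis of variance will be used to determine the intervention effect in the three groups". It then lists the factors: time varies within subject, with pretest as the first of its three levels, and "the between-subjects factor will be group (COG, AE, and SEQ"). No section mentions an MMSE term, a baseline covariate or any other adjustment.

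The same section plans chi-square tests and "analysis of variance to analyze differences in baseline characteristics and baseline outcome measures among the groups". It does not say what would follow from a significant result.

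Under Sample size, the target is 20 evaluable participants per group, with 25 recruited. Under Outcome assessment, MMSE is among the baseline measures, and the outcomes are measured before the intervention.

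**The concern.** Pretest is on the outcome side of the model. Before treatment the randomised arms have no expected difference, so a treatment effect appears as arms changing differently from pretest, that is, in group × time. The contrasts in that interaction that involve pretest are comparisons of change from baseline. Subtracting the whole baseline value is efficient only when r is close to 1. Below that, regression on baseline removes the predictable part of the outcome and adds less noise.

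MMSE governs the allocation but does not enter the analysis. Ignoring a stratifier that is related to the outcome tends to make standard errors too large for the design actually used.

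What is at stake is precision in a trial with about 20 to 25 participants per arm. Both pieces of information are already collected on everyone before treatment.

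**Working it through.** **The plan's own figure.** 20 / (1 − 0.20) = 25 per group, 75 in total, so the attrition step reproduces. The 20 itself cannot be confirmed, because the article does not state the test family, the number of measurements or the correlation used in the power calculation. The point here does not depend on it.

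**Inputs.** The model and its factors come from Analyses, and the stratifier from Study design and setting. The correlation r is not in the article and is assumed over a range. Outcome variance is set to 1 at each visit.

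**One post-treatment visit.**
- Variance of change: 1 + 1 − 2r = 2(1 − r).
- Residual variance after adjusting for baseline: 1 − r².
- Ratio, adjusted over change: (1 − r²) / [2(1 − r)] = (1 + r)/2.

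**Mean of posttest and follow-up, with the same r between every pair of visits (compound symmetry).**
- Variance of the mean of two visits: (1 + r)/2.
- Variance of that mean minus baseline: (1 + r)/2 + 1 − 2r = 1.5(1 − r).
- Residual variance after adjusting for baseline: (1 + r)/2 − r² = (1 − r)(1 + 2r)/2.
- Ratio: (1 + 2r)/3.

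The standard-error ratio is the square root of the variance ratio.

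| r (assumed) | One visit: variance ratio | SE smaller by | Mean of two: variance ratio | SE smaller by |
|---|---|---|---|---|
| 0.5 | 0.75 | 13% | 0.667 | 18% |
| 0.7 | 0.85 | 8% | 0.80 | 11% |
| 0.8 | 0.90 | 5% | 0.867 | 7% |
| 0.9 | 0.95 | 2.5% | 0.933 | 3% |

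In sample-size terms, for the mean of two visits, a change-score comparison needs 20 × 3/(1 + 2r) per group to match a baseline-adjusted analysis with 20. That is 30 at r = 0.5, 25 at 0.7, about 23 at 0.8 and about 21 at 0.9.

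**MMSE.** Baseline MMSE does not vary over time. A stable effect of MMSE raises or lowers all of a participant's visits alike, so it cancels from group × time. It would matter there only if MMSE predicted change. Once the outcome's own baseline is in the model, a further 3% off the standard error would need MMSE to explain 1 − 0.97² ≈ 6% of the remaining variance. A range of 0–3% is a judgement, because the article gives no figure for it.

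**Baseline tests.** If about 30 baseline measures were tested at 0.05, about 30 × 0.05 = 1.5 would be expected to differ by chance. The article attaches no action to such a result.

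**The case against.** The strongest reply has three parts.

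*Covariates are commonly settled in the analysis plan, which is not shown.* This stands in part. Silence about an MMSE term alone could be deferral. The place of pretest could not: the article states outright that it is a level of the within-subject factor, so a later document would have to change the model to adjust for it.

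*The loss may be small.* This stands. Participants are at least 6 months after stroke, and several measures are described as having good or excellent reliability, so r could be high and the saving only a few per cent. On the other side, the eligibility limits (MMSE at least 19, MoCA below 26) restrict the range and could lower r for MoCA, as could the 6-month interval. The documents do not decide between these.

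*The baseline tests do no harm as written.* This also stands. No covariate selection or model change is tied to them.

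Three stronger readings are tempting but unsupported:
- A reader might infer that MMSE was chosen because it predicts the cognitive outcomes, and that leaving it out costs 5–16% of the standard error (√0.90 = 0.949 and √0.70 = 0.837, if it explained 10–30% of outcome variance). The article states no such reason. The figure applies only where no other baseline information is used, so it does not describe group × time, where a stable MMSE effect cancels.
- A reader might infer a large power deficit. With 20 per group, r = 0.5 and one arm better by an assumed 0.6 SD, the planned interaction has about 48% power and the baseline-adjusted analysis about 78%. Part of that gap arises because the interaction test has 4 degrees of freedom. A 2-degree-of-freedom change-score test gives 59%, so only the step from 59% to 78% belongs to this point, and it rests on the assumed effect and correlation.
- A reader might infer that the results would be biased or the type I error inflated. Neither follows. The change comparison is unbiased under randomisation, and omitting a stratifier tends to be conservative.

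**Conclusion.** The point holds as one of efficiency, not validity. As written, the analysis uses baseline as a change score would and leaves out the stratification factor. Adjusting for the outcome's baseline would reduce the standard error by about 13% to 2.5% for one post-treatment visit as r runs from 0.5 to 0.9, and by about 18% to 3% for the mean of two visits. These figures assume equal variances and, for two visits, compound symmetry; r is assumed throughout. Adding MMSE gains perhaps a further 0–3%. The main reason to include it is that the analysis then matches the randomisation. The baseline significance tests answer no useful question in a randomised trial, but they are a minor matter because nothing in the plan hangs on them. The change is worth making because the data are already collected and precision is scarce at this sample size.

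**What to change.** - Take pretest out of the time factor. This must come first: adding the baseline value as a covariate while pretest remains a level of time would put the same measurement on both sides of the model.
- Model posttest and follow-up with group, time and group × time. Pre-specify the baseline value of the same outcome and the MMSE randomisation stratum (or the baseline MMSE score) as covariates. The treatment effect is then read from the group comparison, overall or by visit, and group × time shows whether it differs between the two visits. The rule that triggers Tukey's test needs rewording to match.
- For outcomes with a single post-treatment assessment, such as the blood markers, use the same model without time.
- For outcomes such as grip strength or HbA1c, the article gives no reason to expect MMSE to be prognostic. Its place there rests only on matching the randomisation.
- Present baseline characteristics by arm descriptively, without significance tests, and choose no covariates from observed imbalance.

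The cost is a rewritten model sentence and a few degrees of freedom. The number for an MMSE stratum depends on the cut-points, which the article does not give. No extra participants or measurements are needed. The sample-size text should also be checked against the revised model, since the article does not say which analysis its effect size of f = 0.30 refers to.
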